## Bereavement-related outcomes

### Pre-loss outcomes

Preparedness for patient death: The preparedness for patient death item asks participants “If your care partner were to die soon, how prepared would you be for his/her death?” Response options are “not at all,” “somewhat,” and “very.” This item is based on previous studies of preparedness for loss [44–46]. Preparedness for patient death is measured at T1–T4 in non-bereaved caregivers.Pre-loss grief intensity: The Prolonged Grief-12-Revised (PG-12-R) is a 12-item measure of pre-loss grief, adapted from a measure of prolonged grief symptoms [44] that is worded to reflect the patient as living. PG-12-R items are rated on a 5-point Likert-type scale, with total scores ranging from 11 to 55 and with higher scores suggesting greater anticipatory grief. The PG-12-R has demonstrated strong internal consistency [47] and is administered at T1–T4 to non-bereaved caregivers.Risk for bereavement-related mental health challenges: The Bereavement Risk Inventory and Screening Questionnaire-Pre-Loss (BRISQ-P) is a 30-item screener for bereavement mental health challenges, with items rated on a 5-point Likert scale [48]. The BRISQ-P assesses illness or death-related and bereavement-related risk factors and is administered at T1–T4 to non-bereaved caregivers.Advance care planning engagement: Engagement in advance care planning will be measured by the Advance Care Planning (ACP) Checklist–Current Caregiver [49] which includes 14 items that ask caregivers about previous ACP discussions and domains of ACP (e.g., prognosis, goals of care, execution of advance directives). Items are scored and summed to a total score. This checklist is administered at T1–T4 to non-bereaved caregivers.

### Post-loss outcomes

Post-loss grief intensity: The Prolonged Grief-13-Revised (PG-13-R) is a 13-item measure that evaluates symptoms of prolonged grief disorder [50]. It assesses 10 grief-related symptoms on a 5-point Likert scale. Scores range from 10 to 50 with higher scores indicating greater grief intensity. The PG-13-R is administered at T2–T4 to caregivers who become bereaved during the study.Risk for bereavement-related mental health challenges post-death: The Bereavement Risk Inventory and Screening Questionnaire-Post-Loss (BRISQ-B) is a measure of risk for bereavement mental health challenges following the patient’s death [48]. It is nearly identical to the BRISQ-P, but items are modified to refer to the patient’s death rather than their illness. It also includes items related to the bereavement experience. Items are rated on a 5-point Likert-type scale. The BRISQ-B is administered at T2–T4 to caregivers who become bereaved during the study period.The Presence of Regret: The single Presence of Regret item [22] asks caregivers, “Do you regret any of your actions or choices that occurred while providing care to your loved one with cancer when they were ill?” with a dichotomous yes/no response option. For those who report yes, they will be asked to provide an example of their most troubling regret and to rate their distress about the stated regret on a 10-point scale (10 = most distressed). The Presence of Regret item will be administered at T2–T4 for those caregivers who become bereaved during the study period.Unfinished business: The single unfinished business item asks caregivers, “Do you feel that anything was unfinished, unsaid, or unresolved in your relationship with your loved one with cancer?” with a yes/no response option. If yes, caregivers are asked to provide an example of their most troubling source of unfinished business and to rate their distress about this on a 10-point scale (10 = most distressed). This item was developed to be face valid and consistent with theory on regret and unfinished business [20, 20, 51] and has demonstrated good concurrent validity [21].Advance care planning engagement: Caregivers who become bereaved will complete the Advance Care Planning Checklist–Past Caregiver, which mirrors the Advance Care Planning Checklist–Current Caregiver but asks about what type of care the patient received at end of life, where the patient died, and if the location of death and care provided were consistent with the patient’s stated wishes.

### Plans to promote participant retention and complete follow-up {18b}

Participants will be compensated $10 for each intervention session they complete. They will also be compensated $5 for completing baseline assessments (T1), $10 for completing post-intervention assessments (T2), $15 for completing 6-month follow-up assessments (T3), and $20 for completing 12-month follow-up assessments (T4). Participants are sent a maximum of three emails and called a maximum of three times to remind them to complete each survey. Those participants who discontinue their involvement in the study intervention will be asked to continue to complete study assessments and will receive reimbursement for completed assessments. Participants enrolled through MSK will receive their incentives via Amazon gift card codes and those enrolled through SCCC, via ClinCard.

### Data management {19}

A Clinical Research Coordinator (CRC) is assigned to this study whose responsibilities include project management and compliance, data collection, data entry, data reporting, regulatory monitoring, identifying and resolving problems, and coordinating activities related to the study protocol. The maintained dataset will include minimal data (race, ethnicity, sex, and age) and will be entered into the Clinical Research Administration Clinical Trials Management System.

Data collected for this study will be entered into and managed via the secure Research Electronic Data Capture (REDCap) database. REDCap is an open-source platform that allows for data collection in a secure manner over a web-based interface. The REDCap platform was developed by Vanderbilt University, with whom ISMMS has a standing agreement to allow the usage of REDCap for academic/research purposes. REDCap prevents users from entering data outside of predetermined ranges of possible scores. Participants complete all assessments directly in REDCap, eliminating the need for double data entry of paper assessment forms.

To ensure data quality, reports will be generated periodically to monitor accrual and completeness of participant registration data. Data quality reports will also be generated to assess missing data and inconsistencies. Throughout the study, data on accrual rates and follow-up will be monitored to identify any potential problems that will be brought to the attention of the study team during weekly team meetings. An audit of consent and eligibility data will be performed with the first five enrolled participants to assess for data completeness and data accuracy.

### Confidentiality {27}

Research staff involved in participant recruitment will provide an overview of the study, invite potential participants to participate, and discuss potential risks and benefits during the informed consent process. All participants are required to provide informed consent prior to completing study assessments and the intervention. Participants can choose to skip any question in the assessment battery they do not wish to answer. Participants who report experiencing psychological distress related to completing study questions will be offered support from the enrolling institutions’ counseling or supportive care services or receive community referrals for mental health providers.

When presenting study results, data will be presented for the entire sample and will not reference any individual participant’s data. All survey data will be de-identified using a code number to ensure confidentiality of participant data. For research staff who need to access study data, password security measures and other relevant restrictions will be applied to maintain confidentiality. Confidential data will only be accessible on a “need-to-know” basis for any particular research staff member. All personnel involved with the study will receive training in HIPAA and human subjects’ protections and will receive information on the ethics of accessing electronic data.

### Plans for collection, laboratory evaluation, and storage of biological specimens for genetic or molecular analysis in this trial/future use {33}

No biospecimen data will be collected as part of the study aims and procedures.

## Statistical methods

### Statistical methods for primary and secondary outcomes {20a}

Descriptive statistics will be calculated for baseline demographic and caregiver clinical variables, summarizing each outcome by treatment arm. We will assess the distribution of each study outcome and, if necessary, perform corrective transformations before calculating inferential statistics. We will also perform all efficacy analyses by the intention-to-treat principle, meaning that all randomized participants will be analyzed regardless of dropout or treatment adherence in their respective study arm. All endpoint comparisons between study arms will be adjusted for the randomization stratification variable (study site).

#### Aim 1: Analytic plan

The primary and secondary outcome measures for Aim 1 are all continuous variables assessed repeatedly over the four time points: baseline (T1), immediately posttreatment (T2), 6-month follow-up (T3), and 12-month follow-up (T4). The co-primary efficacy endpoints for Aim 1 are the LAP-R PMI and FACIT SWBS at the immediately posttreatment assessment (T2). We will consider MCP-C efficacious if MCP-C participants have significantly greater improvements than SP-C participants in LAP-R PMI or FACIT SWBS scores at T2 at the *p*< 0.025 statistical significance threshold in the analysis described below. We will analyze each continuous primary and secondary outcome measure by using constrained linear mixed model (cLMM) regression [52–54]. This statistical method accounts for within-subject correlations due to repeated measurement of participants and, under the reasonable missing at random (MAR) assumption, allows unbiased estimation of between-group differences without excluding participants with missing follow-up data. Each of these outcome measures will be analyzed using a separate cLMM regression with random intercept that will model the baseline and repeated follow-up scores (dependent variable) as a function of time (categorical) and the time-by-arm interaction, controlling for the randomization stratification variable (study site). The cLMM method will also constrain the two study arms to have a common baseline mean on the outcome measure to reflect the pre-randomization nature of the baseline assessment (T1) [52]. All randomized participants will have, at a minimum, the baseline (T1) primary outcome assessments and will be included in the cLMM per the intention-to-treat principle. In the cLMM parameterization, the coefficients for the time-by-arm interaction are equivalent to the differences between arms in outcome measure score changes from baseline to the post-baseline time points, and they will be calculated with 95% confidence intervals (CIs). For each co-primary endpoint (LAP-R PMI and FACIT SWBS), we will conclude that MCP-C participants had significantly larger improvements in the endpoint at T2 compared to SP-C if the time-by-arm interaction coefficient for T2 is significantly larger than 0 at the *p* < 0.025 level. The secondary outcome measures will be compared between study arms using similar cLMM analyses. However, we will assess estimated treatment effects at each timepoint using 95% CIs instead of *p*-values.

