### Participant timeline {13}

Potential participants will be screened for eligibility (approximately 5 min) and will meet criteria if they report distress ≥ 4 on the distress thermometer and indicate that the distress is related to caregiving. If interested, participants will complete informed consent procedures and will be offered to immediately complete baseline (T1) assessments. Participants will have up to 45 days (consent expiration) to complete baseline assessments. Once baseline assessments are complete, they will be randomized to either MCP-C or SP-C and assigned to a therapist for seven individual sessions that will be completed over Webex. Participants will have up to 14 weeks to complete all seven sessions. After intervention completion, participants will complete follow-up assessments immediately posttreatment (T2, +2 weeks), 6-month follow-up (T3, ±4 weeks), and 12-month follow-up (T4, ±8 weeks). See Fig. 1 for the full study timeline.

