### Sample size {14}

Participants will be 200 caregivers recruited across study sites and the community, with 100 caregivers randomized to each study arm (MCP-C vs. SP-C). The sample size was chosen to provide 80% power to detect reasonable treatment effect sizes for our two primary endpoints while maintaining the type 1 error rate at *α*= 0.05 for these comparisons. Using methods relevant to clinical trials with repeated measures [31], we calculated the smallest effect size that we will be able to detect for the immediate posttreatment coefficient of the time-by-arm interaction term in our linear mixed model analysis of one of the two primary outcome measures (LAP-R PMI). Given the sample size (*N* = 200), we will be able to detect a standardized mean difference treatment effect size between the two study arms of 0.48 standard deviations. This calculation assumed a correlation between baseline and follow-up measures of 0.5, 20% attrition by the posttreatment assessment, a two-sided significance test, and a type 1 error of 0.025 (0.05 overall for both primary endpoints).

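### The random-intercept model for the co-primary outcomes imposes one variance and one correlation on four unequally spaced visits; if these differ by visit, the standard error of the T2 contrast can be wrong in either direction, and an unstructured covariance avoids this at almost no cost

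*Protocol article*

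**What the plan says.** The Aim 1 plan uses one constrained linear mixed model per outcome: "Each of these outcome measures will be analyzed using a separate cLMM regression with random intercept". Time is categorical with a time-by-arm interaction, study site is a covariate, and the model will "constrain the two study arms to have a common baseline mean on the outcome measure". Superiority on a co-primary endpoint is concluded "if the time-by-arm interaction coefficient for T2 is significantly larger than 0 at the" 0.025 level. Secondary outcomes get similar models, read through 95% confidence intervals. The section names no visit-specific variances, random slope, correlated residuals or robust standard error.

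On timing, the Participant timeline says: "Participants will have up to 14 weeks to complete all seven sessions". T2 follows treatment, with follow-ups at 6 and 12 months. If all 14 weeks are used, T1 to T4 spans about 15 months.

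The Sample size section gives the only covariance figure: "This calculation assumed a correlation between baseline and follow-up measures of 0.5". It also assumes 20% attrition by T2, "a two-sided significance test, and a type 1 error of 0.025 (0.05 overall for both primary endpoints"), and a detectable difference of 0.48 SD with 200 caregivers.

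**The concern.** A random intercept with ordinary independent residuals forces every visit to have the same variance and every pair of visits the same correlation. The T2 contrast with a common baseline mean depends only on the baseline variance, the T2 variance and the T1-T2 correlation. The model replaces these with averages over all four visits, so T3 and T4 data help set the standard error of an endpoint they do not belong to.

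There are reasons to doubt equality here. The gaps between visits differ, T1 precedes treatment while T2 to T4 follow it, and the Aim 3 plan expects about 25% of caregivers to be bereaved by T4.

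At stake is the error rate of both primary tests. Efficacy is declared if either endpoint succeeds, so overall control at 0.05 rests on each test holding 0.025. In the other direction, power is lost. The secondary confidence intervals come from similar models and carry the same dependence.

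**Working it through.** **Inputs from the article.** 100 per arm; 20% attrition at T2, so 80 per arm; baseline/follow-up correlation 0.5; two-sided 0.025 (z = 2.2414); 80% power (z = 0.8416).

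**The plan's own figure.** Without the baseline constraint, keeping all baselines:

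- Variance = 2[(1 − 0.5²)/80 + (1 − 0.5)²/100] = 0.02375, so SE = 0.1541.
- Detectable difference = (2.2414 + 0.8416) × 0.1541 = 0.475, which rounds to the stated 0.48.

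With the common baseline mean that the analysis uses, variance = 2(1 − 0.5²)/80 = 0.01875, SE = 0.1369, and the detectable difference is 0.42. So 0.48 reproduces and is conservative for this model.

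**Effect of the covariance assumption.** Let s² and r be the variance and correlation of the compound-symmetry model that best fits the true covariance (minimum expected Gaussian deviance). With monotone dropout, for the T2 coefficient:

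- Model SE² = 2s²(1 − r²)/80
- True SE² = 2(σ₂² − 2rσ₁₂ + r²σ₁²)/80
- True error = 2[1 − Φ(2.2414 × model SE / true SE)]

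Here σ₁² and σ₂² are the true T1 and T2 variances and σ₁₂ their covariance.

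**Assumed, not in the article.** The true covariances below, and dropout of 20/25/30% at T2/T3/T4, completely at random. Correlations are listed as T1 with T2/T3/T4; then T2-T3/T2-T4/T3-T4. SDs are 1 unless given.

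| Case | True covariance | s² | r | Model SE | True SE | Ratio | True error |
|---|---|---|---|---|---|---|---|
| A | all 0.5 | 1.000 | 0.500 | 0.1369 | 0.1369 | 1.00 | 0.025 |
| B | 0.5/0.4/0.35; 0.5/0.4/0.5 | 1.000 | 0.444 | 0.1417 | 0.1372 | 1.03 | 0.021 |
| C | 0.7/0.55/0.45; 0.65/0.55/0.65 | 1.001 | 0.596 | 0.1270 | 0.1141 | 1.11 | 0.013 |
| D | 0.5/0.45/0.4; 0.7/0.65/0.7 | 0.999 | 0.564 | 0.1305 | 0.1373 | 0.95 | 0.033 |
| E | 0.5 with T1; 0.75 among follow-ups | 0.999 | 0.620 | 0.1240 | 0.1382 | 0.90 | 0.044 |
| F | as D, SDs 1/1.2/1.2/1.2 | 1.287 | 0.560 | 0.1485 | 0.1644 | 0.90 | 0.043 |
| G | as D, SDs 1/1.2/1.1/1 | 1.149 | 0.562 | 0.1402 | 0.1644 | 0.85 | 0.056 |
| H | all 0.5, SDs 1/1/1.2/1.3 | 1.237 | 0.482 | 0.1541 | 0.1370 | 1.125 | 0.012 |

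Case E in full:

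- Model SE² = 2 × 0.999 × (1 − 0.620²)/80 = 0.01537.
- True SE² = 2 × (1 − 2 × 0.620 × 0.5 + 0.620²)/80 = 0.01911.
- Ratio 0.1240/0.1382 = 0.897, and 2[1 − Φ(2.010)] = 0.044.

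**Direction.** Decay (B, C) makes the test conservative. Follow-ups that correlate more with each other than with baseline (D, E), and a T2 SD above the average (F, G), make it anti-conservative. Larger SDs only at T3 and T4 (H) make it conservative: power at 0.48 SD is 84%, against 90% with an unstructured covariance.

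**Simulation check.** REML, N = 200, 2,500 replicates, t reference with 158 degrees of freedom. Monte Carlo error is about √(0.025 × 0.975/2500) = 0.003.

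| Case | Error, random intercept | Error, unstructured |
|---|---|---|
| A | 0.0244 | 0.0256 |
| F | 0.0412 | 0.0256 |
| H | 0.0152 | 0.0256 |

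In case A, power at 0.48 SD was 89.2% with the random intercept and 89.0% unstructured. Point estimates showed no bias in any of the three cases. The true SE of the random-intercept estimator is at most about 2% larger than the unstructured one, so the problem is the reported standard error, not efficiency.

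**The case against.** A reader might infer that the primary p-values are wrong. The documents do not support that. They give no visit-specific SDs and no correlations among follow-ups, and the single value of 0.5 is compatible with compound symmetry. If it holds, nothing is lost. Nor does the visit schedule point to false positives: unequal spacing suggests correlation decay, under which the T2 test is conservative. The inflated cases need further assumptions about the follow-ups. Selection does not supply them, because eligibility uses a distress score, not either co-primary outcome. These points stand, and the concern is conditional and two-sided.

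A reader might also infer that the estimate is biased under missing-at-random dropout. No material bias has been shown. The simulation relied on here covers only dropout completely at random, so no such claim is made.

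The loss of power is limited too. In case C, power at 0.48 SD is about 96% against 98%, and case H still exceeds the planned 80%.

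Finally, a random intercept can be combined with heterogeneous residuals or robust standard errors, and an analysis plan not shown may say so. That is possible. However, the article states a covariance choice for the primary model, and read plainly that choice is compound symmetry. An analysis plan that kept it would keep the restriction.

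**Conclusion.** The point holds as a conditional one. The stated model imposes a restriction that the primary contrast does not need and that cannot be verified in advance. If variances or correlations differ by visit, the nominal 0.025 test at T2 can have a true error of about 0.01 to 0.055, with the direction unknown beforehand. If both co-primary tests ran at 0.044, the bound on the overall error would be 2 × 0.044 = 0.088 instead of 0.05.

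These figures rest on assumed covariances and assumed dropout after T2, and on standard errors being model-based with independent residuals of equal variance. The 0.48 SD stands. This is a cheap improvement to a legitimate model, not the correction of a demonstrated error.

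**What to change.** In the Aim 1 plan, replace the random intercept with an unstructured 4x4 within-participant covariance. Keep the common baseline mean, categorical time, time-by-arm terms and site, and fit by REML with Kenward-Roger degrees of freedom. Prespecify what follows if the model does not converge, for example the random-intercept model with robust standard errors. Apply the same wording to the secondary outcomes.

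The cost is 10 covariance parameters instead of 2, about 0.2 points of power if compound symmetry is true, and a small convergence risk that the fallback covers. The sample size need not change. The article expects recruitment to run until March 2028, so the change can be fixed before the analysis.

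### The two co-primary T2 effects are tested at two-sided p<0.025 but reported with 95% intervals, so an interval can exclude zero beside a non-significant verdict (minor).

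*Protocol article*

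**What the plan says.** Protocol article, Aim 1: Analytic plan. Success on either endpoint is enough: the treatment counts as efficacious if its participants show "significantly greater improvements than SP-C participants in LAP-R PMI or FACIT SWBS scores", judged "at T2 at the *p*< 0.025 statistical significance threshold in the analysis described below". The rule is repeated for each endpoint separately, where a benefit over the comparator is declared only "if the time-by-arm interaction coefficient for T2 is significantly larger than 0 at the *p* < 0.025 level".

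Protocol article, Sample size {14}. The calculation assumes "a two-sided significance test, and a type 1 error of 0.025 (0.05 overall for both primary endpoints".

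Protocol article, Aim 1: Analytic plan, on the time-by-arm coefficients of every primary and secondary model: "they will be calculated with 95% confidence intervals (CIs". The T2 coefficient in the two primary models is the quantity that is tested, so this sentence sets its interval level as well. The article gives no other level for the co-primary effects.

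For the secondary outcomes only, the plan adds: "we will assess estimated treatment effects at each timepoint using 95% CIs instead of *p*-values".

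**The concern.** Because either endpoint can carry the efficacy claim, the plan splits 0.05 into 0.025 and 0.025. The matching two-sided interval for each endpoint is a 97.5% interval. The plan fixes 95% instead, so for a band of results the test and the interval disagree: the text would report no significant difference and the table would show an interval clear of zero. The same section asks readers to judge secondary outcomes from 95% intervals, which makes it easy to read the primary intervals in the same way. At stake is a clear report of the main result. The efficacy decision itself is not affected.

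**Working it through.** **Inputs from the sample size section:** 100 per arm; 20% attrition by T2, so 80 per arm observed; baseline to follow-up correlation 0.5; two-sided 0.025; 80% power; stated detectable effect 0.48 SD. The article does not state a standard error, so a range is used, in units of the outcome SD.

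**Standard error of the T2 coefficient**

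- Constrained model (common baseline mean, as in the Aim 1 plan): SE = √(2 × (1 − 0.5²)/80) = √(2 × 0.75/80) = 0.137.
- Mixed model without the baseline constraint, baseline on 100 and T2 on 80 per arm: variance per arm = 0.75/80 + 0.25/100 + 1/100 − 2 × 0.5/100 = 0.011875; SE = √(2 × 0.011875) = 0.154.

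**The plan's own figure.** Detectable effect = (2.2414 + 0.8416) × SE = 3.083 × SE.

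- SE 0.154 gives 0.475, which rounds to the stated 0.48.
- A change score on 80 per arm (SE = √(2/80) = 0.158) gives 0.487, close to it.
- SE 0.137 gives 0.42.

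The stated 0.48 thus agrees with a two-sided test at 0.025. A one-sided 0.025 test has multiplier 1.9600 + 0.8416 = 2.8016 and gives 0.38, 0.43 and 0.44 for SEs of 0.137, 0.154 and 0.158. None of these is 0.48.

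**Where test and interval disagree.** The 95% interval excludes zero when |z| > 1.960. The test succeeds only when |z| > 2.241. The conflict band on the estimate scale is 1.960 × SE to 2.241 × SE:

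- SE 0.137: 0.268 to 0.307 SD
- SE 0.154: 0.302 to 0.345 SD

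Example with z = 2.10 and SE 0.154: two-sided p = 0.036, estimate 0.324. The 95% interval is 0.022 to 0.626 and excludes zero. The 97.5% interval is −0.022 to 0.669 and includes it. The endpoint fails its test.

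**Chance of landing in the band, per endpoint.** For true effect d, P = Φ(2.241 − d/SE) − Φ(1.960 − d/SE), plus the opposite tail, which matters only near d = 0.

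| True effect (SD) | SE 0.137 | SE 0.154 |
|---|---|---|
| 0 | 2.5% | 2.5% |
| 0.30 | 11.2% | 11.1% |
| 0.42 | 7.0% | 9.2% |
| 0.48 | 4.2% | 6.7% |

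**Joint coverage of the two co-primary intervals.** Two 95% intervals cover both true effects with probability 0.95² = 0.9025 if the endpoints are independent, 0.909 at correlation 0.5 and 0.917 at 0.7. The correlations are assumptions; the article gives none. Two 97.5% intervals cover both with probability of at least 1 − 2 × 0.025 = 0.95 at any correlation.

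**Cost in width.** 2.2414/1.9600 = 1.144, so 97.5% intervals are about 14% wider.

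**The case against.** **The plan decides by p-value, not by interval.** This stands. Efficacy is tied to p<0.025 twice, and intervals replace p-values only for secondary outcomes. A reader might infer that overall error rises to between 8.3% (correlation 0.7) and 9.75% (independence). That would be the error of declaring success whenever either 95% interval excludes zero, a rule that the document does not contain.

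**The interval sentence is general.** Eight Aim 1 outcomes at three follow-ups give 8 × 3 = 24 contrasts. Only two are formally tested, and for the other 22 a 95% level is unobjectionable. An unadjusted 95% interval is also a valid interval for a single parameter. Both points limit the concern but do not remove it: the sentence does fix the level for the two tested coefficients, with no label to say that they are unadjusted.

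**A one-sided reading would remove the mismatch.** The phrase about a coefficient being larger than 0 could suggest a one-sided 0.025 test, which a two-sided 95% interval matches. The sample size section rules this out: it says two-sided, and its 0.48 SD reproduces on that basis.

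**The fixed split might itself look wasteful.** A reader might infer that testing each endpoint at 0.025 even after the other has succeeded is an error. It is not: the equal split is valid, it underlies the sample size, and Holm would leave the chance of at least one success unchanged.

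**Conclusion.** The mismatch is real and minor. Each co-primary T2 coefficient is tested at two-sided 0.025 and reported at 95%, so results with p from 0.025 up to 0.05 would be presented with an interval that contradicts the stated conclusion. The chance per endpoint is about 11% at a true effect of 0.30 SD and 4 to 7% at the protocol's 0.48 SD. These figures rest on a normal approximation and on an SE of 0.137 to 0.154, which follows from the protocol's correlation and attrition but is not stated there. The two 95% intervals also lack joint 95% coverage. The documents support neither a claim that the trial's type 1 error is inflated nor a claim that the alpha split is faulty: the planned test holds 5% overall.

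**What to change.** Report 97.5% confidence intervals for the two co-primary T2 time-by-arm coefficients. Keep 95% intervals for the secondary outcomes and for the exploratory T3 and T4 contrasts. If 95% intervals are also shown for the co-primaries, label them as unadjusted and not used for the efficacy conclusion.

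The cost is one sentence of wording and two intervals that are about 14% wider. The sample size, power, model and data collection stay as they are.

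Holm is not needed for this correction. It could be offered separately as an optional gain in power to claim the second endpoint: at a true effect of 0.42 SD on both endpoints, SE 0.137 and an assumed correlation of 0.5, simulation puts the chance of claiming both at 77%, against 68% under the fixed split. The caveat is that Holm has no simple matching simultaneous intervals. Fixed 97.5% intervals beside Holm would create the reverse conflict, an endpoint declared significant at p between 0.025 and 0.05 with an interval that includes zero.
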